#### Clinical Outcomes

Clinical outcomes (Multimedia Appendix 2) examining the effectiveness of convers-ABI-lity will be collected in a parallel study. As interact-ABI-lity and social-ABI-lity are educational interventions, their effectiveness will be examined by measuring knowledge through preintervention, postintervention, and follow-up multiple-choice questions.

### Analysis

#### Qualitative

To examine effectiveness, 2 experienced speech-language pathologists will review the lists of strategies generated by users of the social-ABI-lity and interact-ABI-lity courses, and code them as appropriate or inappropriate using a consensus rating procedure (Multimedia Appendix 2). To examine implementation, the first author (MM) will conduct deductive content analysis [45] based on the NASSS framework [34] of both free-text survey responses and interview data (Multimedia Appendix 1). Coding will be managed in NVivo 12 Pro (QSR International Pty Ltd) [46] or Microsoft Excel 2016 [47] (Microsoft Corporation) software.

#### Quantitative

We will prospectively measure implementation outcomes in relation to the following:

Preemptive strategies deployed to support the implementation of the Social Brain Toolkit at launch, devised through current implementation evidence [39] and stakeholder input from a separate study [38].Additional user-identified strategies subsequently obtained through formative evaluation of the interventions by end users.

To observe any potential influence of these implementation strategies and factors on implementation success and the time lag of impact, we will record the following:

A detailed description of each implementation strategy and its rationale.A detailed timeline of each strategy’s deployment.Effectiveness and implementation outcomes over time.

We will calculate descriptive statistics of implementation measures, including user demographic characteristics, satisfaction ratings, percentage completion, and total number of users (Multimedia Appendix 1). We will tabulate descriptive statistics stratified by time and by whether users complete the interventions. Descriptive statistical analysis will be conducted using RStudio software (RStudio Inc) [48].

Clinical assessment data for conversation skills and quality of life (Multimedia Appendix 2) [40-42] will be analyzed using the Reliable Change Index [49] to determine whether individual participants had any clinically significant changes. Patient-reported outcome measures for interact-ABI-lity and social-ABI-lity, such as self-ratings of confidence, will be analyzed using repeated measures analysis of variance, with 3 levels (pretraining, posttraining, and follow-up) to determine whether there is any significant improvement within this participant sample. These data will also be managed using appropriate statistical software such as Microsoft Excel 2016 (Microsoft Corporation) [47].

Finally, theoretically underpinned by the third domain of the NASSS framework [34] examining the value proposition of an intervention, we will use the web analytics data for each intervention to calculate web-based health care costs and equivalent face-to-face costs using a bottom-up costing approach [50]. With an initial focus on the Australian context from which the Social Brain Toolkit is developed, we will refer to nationally recognized cost guides such as the Australian Medicare Benefits Scheme [51] to obtain relevant unit costs. Costs will be calculated in Australian dollars, with equivalent conversions reported in euros and US dollars, using RStudio software (RStudio Inc) [48].

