**Methods:**

This is a mixed methods, prospective, hybrid type 2 implementation-effectiveness study, theoretically underpinned by the Nonadoption, Abandonment, Scale-up, Spread, and Sustainability (NASSS) framework of digital health implementation. We will document implementation strategies preemptively deployed to support the launch of the Social Brain Toolkit interventions, as well as implementation strategies identified by end users through formative evaluation of the Social Brain Toolkit. We will prospectively observe implementation outcomes, selected on the basis of the NASSS framework, through quantitative web analytics of intervention use, qualitative and quantitative pre- and postintervention survey data from all users within a specified sample frame, and qualitative interviews with a subset of users of each intervention. Qualitative implementation data will be deductively analyzed against the NASSS framework. Quantitative implementation data will be analyzed descriptively. We will obtain effectiveness outcomes through web-based knowledge tests, custom user questionnaires, and formal clinical tools. Quantitative effectiveness outcomes will be analyzed through descriptive statistics and the Reliable Change Index, with repeated analysis of variance (pretraining, posttraining, and follow-up), to determine whether there is any significant improvement within this participant sample.

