### Aims

In this study, formative evaluation of the implementation of the Social Brain Toolkit by end users in the community will be used to guide intervention development and implementation [37] to support these interventions to reach and meet community needs in a feasible, scalable, sustainable, and acceptable manner. Therefore, guided by domains of the NASSS framework [34,35], in this hybrid implementation-effectiveness study, we aim to answer the following implementation questions:

Who uses these interventions and what are their characteristics (domains 1 and 4)? What implementation strategies can be used to improve intervention reach?In what geographical locations and health care and social contexts are the interventions used (domains 3 and 5-6)? What implementation strategies can be used to improve intervention reach?Do users complete the interventions as intended (domain 4)? Why or why not? What implementation strategies can be used to improve intervention adherence and fidelity?How usable is the technology for those completing the interventions (domain 2)? What changes can be made to improve usability?What barriers, facilitators, and workarounds do users experience when completing these interventions (domains 1-7)? What strategies, facilitators, and workarounds can be used to improve future implementation?How satisfied are users with the interventions (domain 3)? What changes can be made to increase user satisfaction?What is the cost of delivering each web-based intervention, and how does this compare with face-to-face delivery (domain 3)?

We seek to determine intervention effectiveness as follows:

Do people who complete the interact-ABI-lity course have improvements in their self-efficacy and knowledge about communicating with people with ABI?Do people who complete the social-ABI-lity course have improvements in their self-efficacy and knowledge about communicating safely and successfully on social media?Do people who complete the convers-ABI-lity program have improved communication and quality-of-life outcomes?

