#### Inclusion and Exclusion Criteria for Users of convers-ABI-lity

Interviews will be conducted with all 10 people with ABI and their 10 communication partners who have completed the pilot version of convers-ABI-lity, as well as the 5 clinicians delivering the intervention. Participants with ABI must meet the following criteria:

They must have had a definite moderate-severe ABI at least 6 months previously based on the Mayo Classification Scheme [56] (at least one of the following: loss of consciousness of 30 minutes or more, posttraumatic amnesia lasting ≥24 hours, worst Glasgow Coma Scale total score in the first 24 hours of <13, or evidence of a significant brain imaging abnormality). People with a non–traumatic brain injury (restricted specifically to the etiologies of stroke, hypoxic injury, brain tumor, poisoning, and infection) will also be eligible to participate.They must have been discharged or partially discharged from hospital and be able to spend time at home on a regular basis.They must have significant social communication skills deficits (either self-identified or identified by a usual communication partner).They must have insight into their social communication skills deficits.They must be aged 18-70 years.They must have adequate English proficiency for completing assessment tasks without the aid of an interpreter.They must have functional reading skills in English.They must have a communication partner with whom they interact regularly who is willing to participate in the research interviews and training program.

The exclusion criteria for participants with ABI are as follows:

Aphasia of a severity such that it prevents any participation in conversation.Severe amnesia, which would prevent participants from providing informed consent, as evaluated using the University of California, San Diego, Brief Assessment of Capacity to Consent instrument [55].Dysarthria of a severity such that it significantly reduces intelligibility during conversation, as evaluated by the researcher.Drug or alcohol addiction, which would prevent participants from reliably participating in sessions.Active psychosis.Co-occurring degenerative neurological disorder, more than one episode of moderate-severe ABI, or premorbid intellectual disability.

Family members, friends, or paid support workers participating in the study must meet the following criteria:

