## Discussion

### A Dual Focus on Implementation and Effectiveness

As the global burden of ABI grows, our communities and health care system must find a scalable, feasible, acceptable, and accessible health care service delivery solution to address the psychosocial burden of this condition [1]. A concerted focus on implementation is essential to ensure the successful and sustained uptake of health interventions, without which even efficacious treatments have failed to be adopted, implemented, or sustained [29]. Implementation knowledge should include the perspectives of key stakeholders, while also leveraging existing implementation science theory and evidence, to ensure implementation success.

To this end, we have selected several theoretically informed implementation measures, in addition to measuring the effectiveness of the Social Brain Toolkit. As social-ABI-lity and interact-ABI-lity are educational interventions, their effectiveness will be determined through measures of increased knowledge as well as ecologically valid postintervention measures such as frequency of social media use and confidence communicating with people with ABI. For the CPT intervention of convers-ABI-lity, effectiveness is determined by similarly meaningful measures of quality of life and conversation. The complexity of real-world implementation will be captured using mixed methods, including surveys and interviews exploring user satisfaction and experiences of implementation. For example, our specific survey of whether users are from rural, regional, remote, or metropolitan areas will enable the implementation experiences of these populations to be compared. Given the web-based nature of the Social Brain Toolkit, implementation measures will also include web analytics to identify any need for targeted implementation adjustments or strategies to improve intervention use. As the Social Brain Toolkit comprises technological interventions, think-aloud methods will be used to explore technological usability and provide users with a direct feedback channel to improve user interfaces.

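### The Reliable Change Index is said to show clinically significant change in convers-ABI-lity participants, but on its own it shows only change beyond measurement error

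*Protocol article*

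**What the plan says.** Under Analysis, Quantitative, the article takes "Clinical assessment data for conversation skills and quality of life" and states that they "will be analyzed using the Reliable Change Index [49] to determine whether individual participants had any clinically significant changes". The Discussion (A Dual Focus on Implementation and Effectiveness) ties these two domains to one intervention: "For the CPT intervention of convers-ABI-lity, effectiveness is determined by similarly meaningful measures of quality of life and conversation".

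Four other places bear on the point:

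- **Aims** puts the effectiveness question for this intervention as "Do people who complete the convers-ABI-lity program have improved communication and quality-of-life outcomes".
- **Analysis, Quantitative** gives the other two interventions a group-level test: "Patient-reported outcome measures for interact-ABI-lity and social-ABI-lity, such as self-ratings of confidence, will be analyzed using repeated measures analysis of variance, with 3 levels".
- **Abstract, Methods paragraph** does not divide the analyses by intervention: "Quantitative effectiveness outcomes will be analyzed through descriptive statistics and the Reliable Change Index, with repeated analysis of variance (pretraining, posttraining, and follow-up".
- **Clinical Outcomes** says where the data come from: "Clinical outcomes (Multimedia Appendix 2) examining the effectiveness of convers-ABI-lity will be collected in a parallel study".

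The article states no index cut-off, reliability, SD, minimal important difference or normative range for these measures.

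**The concern.** The index divides one person's change by the standard error of a difference between two measurements. Passing it means that the change is unlikely to be measurement noise. It does not mean that the change matters to the person. A small change can pass on a very reliable instrument, and an important change can fail on a noisy one. The sentence in the Quantitative section therefore gives the method a conclusion that it cannot deliver alone. Read literally, each participant who passes could be reported as having changed to a clinically significant degree.

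A second, weaker issue is fit to the aim. The Aims ask whether people who complete the program improve, which is a question about the group. A count of individuals who pass a noise threshold is an indirect answer: it can include chance improvers, and it can miss a modest improvement shared by everyone.

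**Working it through.** The article gives no figure for this analysis, so there is nothing to reproduce. The numbers below are illustrations.

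**Inputs**
- Cut-off 1.96: assumed (conventional).
- Reliability r: assumed, range 0.70 to 0.95.
- n = 10: taken from the interview paragraph of the convers-ABI-lity criteria ("all 10 people with ABI and their 10 communication partners who have completed the pilot version of convers-ABI-lity"). Its use for the clinical outcomes is an assumption, because no sample size is stated for the parallel study.

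**Step 1. What the threshold depends on.** RCI = change / (SD × √(2(1 − r))). The change needed, in baseline SD, is 1.96 × √(2(1 − r)):

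| r | √(2(1 − r)) | change needed (SD) |
|---|---|---|
| 0.70 | 0.775 | 1.52 |
| 0.80 | 0.632 | 1.24 |
| 0.90 | 0.447 | 0.88 |
| 0.95 | 0.316 | 0.62 |

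No term in the formula carries clinical importance. A 1.0 SD change passes at r = 0.90 and fails at r = 0.80.

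**Step 2. Chance improvers.** With no true change, each person has probability 0.025 of passing in the direction of improvement.
- Expected number among 10, per measure: 10 × 0.025 = 0.25.
- At least one among 10 on one measure: 1 − 0.975^10 = 0.22.
- At least one over two measures, if independent (one for each domain named): 1 − 0.975^20 = 0.40. Positive correlation between the measures would lower this.

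**Step 3. Individual classification against a group estimate.** Suppose all 10 people truly improve by 0.5 SD and change scores vary only through measurement error. The chance that a given person passes is 1 − Φ(1.96 − 0.5/√(2(1 − r))). The power of a two-sided 5% paired t-test comes from the noncentral t distribution with 9 degrees of freedom.

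| r | person passes | paired test power |
|---|---|---|
| 0.70 | 9% | 45% |
| 0.80 | 12% | 61% |
| 0.90 | 20% | 88% |
| 0.95 | 35% | 99% |

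Real variation between people in their response would lower the power figures.

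**Step 4. Precision of a mean change.** The 95% CI half-width for n = 10 is t(9, 0.975)/√10 = 2.262/3.162 = 0.72 SD of the change scores.

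**The case against.** The article says openly that the index is for individual participants and does not present it as a test of group benefit. Classifying individuals is a legitimate choice in a small pilot. The source cited for the index and Multimedia Appendix 2 are not shown, so a second criterion may accompany the index in practice. The study is formative and uncontrolled, no confirmatory decision hangs on the result, and its limitations section already acknowledges sample size and self-report.

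Much of this stands. It lowers the severity and makes the numerical illustrations conditional. It does not rescue the sentence, which names the index alone as the means of determining clinical significance.

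A reader might go further and infer that the index is the only analysis planned for convers-ABI-lity. It is not: descriptive implementation statistics, costing for each intervention and coding of interviews also cover it. A reader might also infer that no group estimate will ever be produced. The documents do not establish that. The Abstract can be read as applying descriptive statistics and repeated analysis of variance to all effectiveness outcomes, and the clinical data are collected in a parallel study whose own plan is not shown.

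**Conclusion.** The main point holds: the Quantitative section labels as clinically significant what the index can show only to be reliable change. That follows from the definition of the index and needs no assumption about reliability or sample size. The size of the mismatch does depend on assumptions: at 1.96, the change needed ranges from 1.52 SD (r = 0.70) to 0.88 SD (r = 0.90).

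The secondary point holds in a limited form. Within the Methods body, the index is the only quantitative effectiveness analysis named for convers-ABI-lity, while the aim is a group question and the Abstract's list is wider. This is a discrepancy to reconcile, not proof that a group analysis is absent. Overall severity is moderate.

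**What to change.** 1. In Analysis, Quantitative, replace the reference to clinically significant changes with *reliable change (beyond measurement error)*. Use *clinically significant* only where reliable change is accompanied by a functional cut-off or minimal important difference prespecified for that tool.
2. Reconcile the Abstract's Methods paragraph, Clinical Outcomes and Analysis, Quantitative, so that it is clear which analyses apply to the convers-ABI-lity outcomes and in which study they are reported.
3. Report the paired mean change with 95% CI for each outcome, labelled preliminary, here or in the parallel study.

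The cost is a wording change and a short table from data that are to be collected anyway. The downside is that fewer participants can be called clinically significantly improved, and the interval will be wide: about ±0.72 SD of the change scores if n = 10.

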### Participants

#### Inclusion and Exclusion Criteria for Users of interact-ABI-lity and social-ABI-lity

As social-ABI-lity and interact-ABI-lity are publicly available web-based courses, all users of the courses within the sample frame will be included in data collection and analysis of survey and analytic data, with no restrictions of inclusion and exclusion criteria. A minimum of 5 users of the social-ABI-lity course (ie, people with ABI) and interact-ABI-lity courses (ie, communication partners such as paid support workers, friends, and family members) will be invited to participate in further implementation interviews. This number of users interviewed is consistent with the think-aloud methods described in the study design [43], which are used to refine the usability of the courses. The internationally recognized industry standard [53] is for a minimum of 5 users to undergo a formative usability interview evaluation [53], because only so many users are required to identify up to 90% of the usability issues [54] before there are diminishing returns for the product cycle [53]. However, a maximum variation sample of these interviewees will be sought if and where possible.

If people with ABI completed the social-ABI-lity course with the assistance of a friend, partner, family member, or other individual, this person will also be invited through the course user to be interviewed together or individually, depending on individual preference or availability. Therefore, interview participants must meet the following criteria:

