### Participant Enrollment

At manuscript submission on July 13, 2021, 85 participants had enrolled in interact-ABI-lity, with 85 completed entry surveys, 6 course completions, and 8 completed exit surveys. No interview data had yet been collected. Data collection for interact-ABI-lity commenced on July 2, 2021, and is expected to conclude on January 2, 2022, after a 6-month sample frame of analytics. By July 13, 2021, 1 participant had been recruited to participate in the convers-ABI-lity study, with no data yet collected. Data collection is expected to commence on July 26, 2021, and conclude on March 26, 2022. By July 13, 2021, no participant had been recruited to participate in the social-ABI-lity study. Data collection is expected to commence on December 1, 2021, and conclude on June 1, 2022, after a 6-month sample frame of analytics.

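### The three-level repeated measures ANOVA by default keeps only users with all three scores, a set that is neither all users nor course completers, and its omnibus F does not by itself show improvement

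*Protocol article*

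**What the plan says.** Under Methods, Analysis, Quantitative, the protocol article states that self-rated outcomes for the two educational courses "will be analyzed using repeated measures analysis of variance, with 3 levels (pretraining, posttraining, and follow-up) to determine whether there is any significant improvement". The abstract repeats this for the quantitative effectiveness outcomes: "with repeated analysis of variance (pretraining, posttraining, and follow-up), to determine whether there is any significant improvement within this participant sample". Under Clinical Outcomes, knowledge is also taken at three times, by "measuring knowledge through preintervention, postintervention, and follow-up multiple-choice questions".

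Two other sections describe who is meant to be analysed, and they differ:

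- Inclusion and Exclusion Criteria for Users of interact-ABI-lity and social-ABI-lity: "all users of the courses within the sample frame will be included in data collection and analysis of survey and analytic data".
- Aims: "Do people who complete the interact-ABI-lity course have improvements in their self-efficacy and knowledge about communicating with people with ABI" and, for the other course, "Do people who complete the social-ABI-lity course have improvements in their self-efficacy and knowledge about communicating safely and successfully on social media".

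The only counts are under Participant Enrollment. At submission on July 13, 2021, "85 participants had enrolled in interact-ABI-lity, with 85 completed entry surveys, 6 course completions, and 8 completed exit surveys". No follow-up count and no expected completion or follow-up rate are given.

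**The concern.** A conventional repeated measures ANOVA with one three-level time factor needs a complete row for each user. Someone with entry and exit scores but no follow-up score is removed from the whole analysis, including the pre-post comparison for which the data are in hand. In open, self-directed online courses, some loss between entry, exit and follow-up is to be expected.

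Three things are at stake:

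- **Target.** The users analysed are those who answered three times, which is neither of the groups the article names.
- **Bias and precision.** If answering follow-up is related to the exit score, the pre-post gain among responders differs from the gain among all completers. Even if it is unrelated, observed pairs are discarded.
- **Question answered.** The omnibus F has no direction. A decline, or a rise followed by a fall, can be significant too, while the stated purpose is to detect improvement.

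**Working it through.** The article gives no sample size, SD, effect size or dropout rate for this test, so there is no planned figure to reproduce. The checks below use its counts and, where marked, assumptions.

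**1. What the interim counts show.** Completions: 6/85 = 7.1% (95% CI 2.6 to 14.7%). Exit surveys: 8/85 = 9.4% (4.2 to 17.7%). On timing, "Data collection for interact-ABI-lity commenced on July 2, 2021, and is expected to conclude on January 2, 2022". July 2 to July 13 is 11 days, and July 2 to January 2 is 184 days. On day 11 at least 85 − 8 = 77 users (91%) could not yet have had a pre-post pair, but many may still have been working through the course. There were 8 exit surveys against 6 completions, so, at one survey per user, at least 8 − 6 = 2 came from users not recorded as completers. An exit survey therefore does not identify a completer.

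**2. Possible final loss (assumed shares).** Complete triplets per 85 enrolled = 85 × exit share × follow-up share:

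| Exit share | Follow-up share | Product | Of 85 |
|---|---|---|---|
| 0.3 | 0.5 | 0.15 | 13 |
| 0.5 | 0.7 | 0.35 | 30 |
| 0.7 | 0.7 | 0.49 | 42 |
| 0.7 | 0.9 | 0.63 | 54 |
| 0.9 | 0.9 | 0.81 | 69 |

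Most users are lost only if the product is below 0.5.

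**3. Precision of one paired contrast.** The 95% CI half-width, in SDs of the difference, is t(0.975, n−1)/√n: 0.84 for n = 8, 0.51 for n = 17, 0.31 for n = 43 and 0.22 for n = 85.

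**4. Cost of dropping pre-post pairs among completers.** Assumptions: 100 completers, all with pre and post scores; SD 1; correlations 0.6 (pre-post), 0.5 (pre-follow-up) and 0.6 (post-follow-up); true gains 0.30 at post and 0.20 at follow-up; 50% answer follow-up.

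- *Response unrelated to scores.* The SD of the post-pre change is √(2 × (1 − 0.6)) = 0.894. The standard error is 0.894/√50 = 0.126 for complete cases and 0.894/√100 = 0.089 with all pairs, a ratio of √2 = 1.41. Simulations gave 0.126 against 0.088 and 0.121 against 0.087, so about 40% larger. Both estimates centre on 0.30.
- *Response depends on the post score.* If responders' mean post score lies m SD above that of all completers, the complete-case post-pre gain is 0.30 + (1 − 0.6) × m. A logit slope of 1 per SD gives m = 0.413, hence 0.30 + 0.4 × 0.413 = 0.465. A slope of 1.5 gives m = 0.53, hence 0.512. A slope of −1 gives 0.30 − 0.165 = 0.135. Simulation agrees (0.46, 0.51 and 0.14), and likelihood estimation gives 0.30 in each case. At about 70% response the complete-case values are 0.41 or 0.19.
- With these correlations the follow-up minus pre contrast is unbiased either way. The damage is to the post-pre gain.

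**5. Where a mixed model does not help.** (a) Assumed: 500 enrolled users, random-intercept correlation 0.6, and response driven by the user's stable level (logit slope 1.5). Complete-case changes are about 0.30 and 0.20, which is correct. A likelihood model on all enrolled users gives 0.50 and about 0.48, which is badly biased. (b) Assumed: two time points, true gain 0.30, and response depending on the gain itself, with 10% or 50% observed. Complete cases give 0.59 or 0.46, and the likelihood estimate using all baselines gives 0.48 or 0.40. Both are biased.

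**The case against.** The strongest reply has four parts.

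- **Attrition is not established.** A reader might infer from 85 entry and 8 exit surveys that most enrolled users will be dropped. The document does not support that. The counts are from day 11 of 184, and no final or follow-up rate is given. This part stands in full.
- **The question is about completers.** Leaving non-completers out of the effectiveness test agrees with the Aims, and the Quantitative section confines inference to this sample. This stands, and it rules out making an all-enrolled model the main analysis. It does not rescue the ANOVA, because finishing a course and answering its follow-up are different events.
- **A mixed model is not always safer.** A reader might infer that complete-case change is biased unless scores are missing completely at random, and that missing at random is the weaker requirement. Neither is true: in step 5(a) complete cases are right and the all-enrolled likelihood model is wrong. Neither assumption contains the other.
- **This is analysis-plan detail.** Listwise deletion is nowhere written, and partial-data rules and contrasts may sit in a fuller plan. Reported means would show direction, and a biostatistician can be consulted. This tempers the point. Even so, the article does fix the method, and that method's default conflicts with the article's own account of who is analysed.

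**Conclusion.** The point holds in a limited form. The named test by default analyses only users with all three scores, discards observed pre-post pairs from completers who skip follow-up, and matches neither population the article describes. Its omnibus F does not by itself establish improvement.

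The size depends on the final follow-up response, which is unknown. With half of completers answering follow-up, the illustration gives a standard error about 40% larger. The shift in the post-pre gain is −0.16 to +0.21 on a true 0.30 when response depends on the post score, and zero when response is unrelated to scores. These figures rest on the assumed correlations and response mechanisms, and the direction of any bias cannot be predicted.

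This is a cheap improvement to an uncontrolled formative study that already acknowledges limits of sample size and self-report. It is not an error that must be corrected for the study to stand.

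**What to change.** 1. Define the effectiveness set for each course as completers identified from course records, in line with the Aims, and reconcile the Participants sentence on analysing all users with that definition.
2. Replace the ANOVA with a linear mixed model (time as a three-level categorical effect, within-user covariance) fitted to every available score from that set.
3. Report post minus pre and follow-up minus pre, each with a 95% CI, as the test of improvement.
4. Tabulate entry scores and characteristics of users with and without later scores. The article already plans descriptive tables by completion status for implementation measures, so this extends existing work.
5. Show the result in users with all three scores, and any all-enrolled model, as sensitivity analyses.

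The cost is a change of wording and a few lines of R, which the study already uses for its descriptive statistics. No new data are needed. The downside is that the model assumes scores are missing at random. That is a different assumption from the one complete-case change needs, not a strictly weaker one, and bias can remain if response depends on unobserved gain or on a stable user trait. The sensitivity analyses and the table of responders and non-responders help a reader judge this.
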